## Abstract

**Background:**

Although it was initially assumed that erythropoietin (EPO) was a hormone that only affected erythropoiesis, it has now been proposed that EPO plays an additional key role in the regulation of acute and chronic tissue damage.

Via the inhibition of inflammatory reactions and of apoptosis, stem cell recruitment, advancement of angiogenesis and growth factor release, EPO enhances healing and thus *restitutio ad integrum* after trauma. Human skin contains EPO receptors and is able to synthesize EPO. We therefore hypothesize that EPO is able to optimize wound healing in thermally injured patients.

**Methods/Design:**

This is a large, prospective, randomized, double-blind, multi-center study, funded by the German Federal Ministry of Education and Research, and fully approved by the designated ethics committee. The trial, which is to investigate the effects of EPO in severely burned patients, is in its recruitment phase and is being carried out in 13 German burn care centers. A total of 150 patients are to be enrolled to receive study medication every other day for 21 days (EPO 150 IU/kg body weight or placebo). A follow-up of one year is planned. The primary endpoint of this study is the time until complete re-epithelialization of a defined skin graft donor site is reached. Furthermore, clinical parameters such as wound healing, scar formation (using the Vancouver scar scale), laboratory values, quality of life (SF-36), angiogenic effects, and gene- and protein-expression patterns are to be determined. The results will be carefully evaluated for gender differences.

**Discussion:**

We are seeking new insights into the mechanisms of wound healing in thermally injured patients and more detailed information about the role EPO plays, specifically in these complex interactions. We additionally expect that the biomimetic effects of EPO will be useful in the treatment of acute thermal dermal injuries.

**Trial registration:**

EudraCT Number: 2006-002886-38, Protocol Number: 0506, ISRCT Number: http://controlled-trials.com/ISRCTN95777824/ISRCTN95777824.

## Background

Over the past few years, our understanding of erythropoietin (EPO) has changed significantly. Although it was initially assumed that EPO was a hormone affecting erythropoiesis only
[1], it has now been discussed that EPO plays a key role in the repair of acute and chronic tissue damage. It has also been proposed that EPO has a significant anti-inflammatory effect, whereby the inflammatory response is part of the normal reaction of any organism to injury. Via the inhibition of inflammatory reactions, EPO influences healing and thus promotes *restitutio ad integrum* after trauma
[2].

In addition, EPO seems to be involved in ensuring that stem cells are recruited to the required location. The best-known effect is the endothelial nitric oxide synthase (eNOS) mediated response and the recruitment of endothelial progenitor cells (EPCs)
[3]. *In vitro* data show enhancement of stem cell proliferation and stem cell phenotype-conservation caused by EPO in human mesenchymal dermal stem cells grown under hypoxic conditions and in IL-6 enriched media
[4].

Additionally, there are numerous publications reporting EPO’s function as a protective molecule of capillary endothelial cells, which under hypoxic stress would normally become apoptotic, thus improving the blood supply in the surrounding tissues
[5]. In many tissues, inhibition of apoptosis is induced directly via a phosphorylation cascade initiated by the EPO receptor. Numerous pathways can be attributed to phosphorylation of janus kinase 2 (JAK-2) and subsequent phosphorylation of signal transducers and activators of transcription (STATs) and B-cell lymphoma extra-large (BCL-XL) or are mediated via phosphatidylinositol-3 kinase (protein kinase A) (PI3K-Akt) and mitogen-activated protein kinase (MAPK) pathways
[6,7]. STAT then evokes apoptotic inhibition in the nucleus. Furthermore, Akt (protein kinase B) is activated, which plays a central role in cell survival
[8].

Several authors report that EPO also triggers a variety of growth factors (see Table 
1). Since we are focusing our discussion onto factors which are known to be involved in wound healing, the present work describes a selected number of growth factors and their effects.

**Table 1 T1:** Most important effects of EPO on different growth factors in wound healing

**Factor**	**Action**	**EPO action**	**Tissue, organ, species**	**Reference**
TNF-α	Primary-injury response	Antagonist	Neuronal tissue, brain, mice	[9]
IL-2, -6, -8	Proinflammatory cytokines	Inhibition	Human histiocytic lymphoma cells	[10]
				[11]
γ-interferon	Proinflammatory cytokine	Inhibition	Human histiocytic lymphoma cells	[10]
MIP 1 u. 2	Proinflammatory protein	Inhibition	Cartilage, mice (arthritis model)	[12]
Myeloperoxidase	Invasion-marker for macrophages	Inhibition	Neuronal tissue, brain, mice	[13]
IL-1β	Proinflammatory cytokine	Inhibition	Human histiocytic lymphoma cells	[10]
γ-interferon	Proinflammatory cytokine	Inhibition	Human leucocytes	[14]
VEGF	Angiogenesis	Stimulation	Skin, microvessels, mice	[15]
eNOS	Recruitment of EPCs	Stimulation	Skin, microvessels, mice	[16]
EGF	Angiogenesis	Stimulation	Heart, microvessels, neovasculature, rat	[17]
HIF-1α / HIF-2α	Adaption to hypoxia, stimulation of EPO and VEGF	Stimulation	Human hepatoma cell lines	[18]
EPAS 1	Adaption to hypoxia	Stimulation	Cortical astrocytes	[19]
			Cortical astrocytes	[19]
iNOS	Relaxation of smooth muscle cells	Stimulation	Skin, microvessels, mice	[15]
BCL-Xl	Anti-apoptotic	Stimulation	Erythroid progenitor cell line, mice	[20]
IGF-I	Anti-apoptotic	Stimulation	Astrocytoma cell line	[21]
	cell proliferation			
Caspase-3	Apoptosis	Inhibition	Kidney, rat	[22]
BCL-2	Anti-apoptotic	Stimulation	Erythroid progenitor cell line, mice	[23]
	proliferation			
hsp 70	Intracellular protective processes	Stimulation	Human TF-1 cell line	[24]

BCL: B-cell lymphoma; EGF: endothelial growth factor; eNOS: endothelial nitric oxide synthase; EPAS: endothelial PAS domain-containing protein; EPC: endothelial progenitor cell; hsp: heat shock protein; IGF: insulin-like growth factor; iNOS: inducible nitric oxide synthase; MIP: macrophage inflammatory protein; TNF: tumor necrosis factor; VEGF: vascular endothelial growth factor.

Several publications indicate that the actions of specialized proinflammatory cells, such as leukocytes and macrophages, are down-regulated by EPO: the production of IL-2, IL-6, IL-8, γ-interferon and tumor necrosis factor α (TNF-α) is antagonized
[10,14,25].

Normal human skin contains EPO receptors and is able to synthesize EPO. In culture, under hypoxic conditions, EPO synthesis increases
[26].

In a mouse model the combined presence of EPO receptor (EPOR) and the EPO-hetero-receptor could be demonstrated in healthy and scalded skin. Additionally, after systemic EPO application the EPOR was significantly down-regulated in the healthy skin; by contrast, in the scalded skin, the expression rate stayed unchanged
[27].

Several investigations on the effects of EPO on wound healing have shown predominantly elevated vascular endothelial growth factor (VEGF) and endothelial growth factor levels (and resulting elevated capillary density) in treatment groups compared to controls. This was emphasized by increased cluster of differentiation 31 (CD31) gene expression. Higher protein and collagen densities, as well as the greater mechanical stability of fresh cicatrices, were found in treatment groups as well
[28].

One of the first research projects to examine the effects of EPO on wound healing, used fibrin-filled subcutaneously implanted chambers. These chambers were then injected with an EPO/fibrin mixture with different concentrations of EPO. The formation of granulation tissue was stimulated by the administration of EPO. When an anti-EPO or anti-EPO receptor antibody was added, the formation of granulation tissue deteriorated
[29].

An *in vitro* study examined the effects of EPO and EPO receptors in human hair follicles. It was shown that hair follicle cells produce EPO and EPO receptors and that EPO shows its typical tissue-protective effects. Protective effects against chemotherapy-induced apoptosis of hair follicle cells was demonstrated
[26]. Skin-derived EPO appears to act locally, while it is less important for the systemic EPO response to acute hypoxia in healthy humans
[30].

The effects of subcutaneous EPO on dermal regeneration were also investigated using nude mice. In this model, the healing of a full thickness defect was traced directly into the skin-fold chamber in nude mice. It was shown that with EPO the healing process not only improved but was also accelerated depending on the dosage
[31].

In another mouse model, after thermal trauma and subsequent EPO treatment, improved and accelerated wound healing was observed compared to the control group
[32]. This was marked by increased epithelial proliferation, maturation of the extra-cellular matrix, increased angiogenesis and increased capillary density, identified by high CD31, VEGF values and eNOS activity. When mice were administered anti-EPO antibodies, wound healing deteriorated below that of the control group. After thermal trauma in mice and subsequent EPO treatment, mice exhibited improved and accelerated re-epithelialization as well as faster wound healing compared to control groups. This was characterized by increased epithelial proliferation, and maturation of extra-cellular matrices, as well as increased angiogenesis and capillary density detectable via high CD31 and VEGF values and eNOS activity
[32].

The above findings lead to the assumption that EPO represents a new, effective therapeutic opportunity for the treatment of acute dermal thermal injuries.

## Methods/Design

This study is conducted according to globally accepted standards of good clinical practice (as defined in the ICH E6 Guideline for Good Clinical Practice, 1 May 1996), in agreement with the Declaration of Helsinki and in keeping with local regulations. It has full approval of the designated ethic committee (at the University of Lübeck, [name]) and is funded by the German Federal Ministry of Education and Research. Additionally, the study received support for medication costs from Heraeus Holding GmbH.

### Objectives

The study objectives are to demonstrate a cytoprotective and regenerative effect of erythropoietin in thermally injured patients in terms of reduced morbidity and mortality and to better understand the cellular mechanisms of erythropoietin in skin graft donor sites (SGDSs) and second-degree wounds (SDWs).

### Study design

This is a prospective, randomized, double-blind, multi-center clinical trial, conducted in 13 burn care centers in Germany. In total, 150 adult patients with burn and scald injuries will be included.

Via a centralized randomization list, patients are randomly allocated to the drug- or the placebo-treated group. Patients receive normal state-of-the-art burn care treatment plus study medication every other day. Study wound sites (SGDCs and SDWs) are treated with standard wound dressings. Dressing changes, wound documentation, photo documentation, biopsies, control of safety parameters, study medication and other relevant actions are strictly regulated in the study protocol. The acute treatment and observational phase is 28 days, with follow-up controls at Day 42, after 6 months and 12 months after inclusion.

### Patient population

Adult patients between 18 and 75 years of age with deep burns (deep second (2b) or third degree) or scalding injuries between 5% and 60% of total body surface (TBS) (patients under 40 can have more than a 60% TBS injury), and where a necrectomy and consecutive split skin graft transplantation is indicated, are to be included in the trial. Patients who are either pregnant or breastfeeding are to be excluded. Informed consent in written form must be given before the first study-specific action, by the patient, the patient’s legal representative or via the *Heidelberger Verfahren*. The *Heidelberger Verfahren*, first described by Brückner et al.
[33], allows recruitment of patients who are unable to give informed consent themselves and where there is insufficient time to appoint a legal representative. In such cases, a judge, in consensus with the ethics committee and the judicial court, decides whether a patient can take part in the trial and gives the patient’s next-of-kin the authority to give informed consent on behalf of the patient. However, in cases where a next-of-kin is not available or unknown, the judge has the legal authority to give informed consent in advance and simultaneously a legal representative will be designated, who will subsequently give informed consent. Additionally as soon as the patient is able to give informed consent, he or she will be asked to do so.

### Inclusion criteria

3° burn and scalding thermal injuries obligate, 2° burn and scalding thermal injuries optional, which require operations including split skin harvesting and grafting

Men and women, age ≥ 18 and ≤ 75 years

Secure contraception.

### Exclusion criteria

Admission later than 24 hours after injury.

Hematological disorders (anemia, lymphoma, leukemia, inborn coagulation diseases).

Pregnancy or breast-feeding.

Estimated survival shorter than one week (abbreviated burn severity index (ABSI) > 12) in patients older than 40 years of age.

Body weight < 50 kg or > 110 kgTotal burn surface area involved less than 60% in patients older than 40 years of age.

In patients below 40 years of age no limitation of maximum burned body surface and no limitation of ABSI score will be considered.

Upper lateral thighs of both legs thermally injured.

Subject is the investigator or any sub-investigator, research assistant, pharmacist, study coordinator, other staff or relative thereof directly involved in the conduct of the protocol.

Subject is unlikely to comply with protocol, e.g., uncooperative attitude, inability to return for follow-up visits, and unlikelihood of completing the study.

Treatment with any investigational product in the last 12 months before study entry.

Treatment with any immunosuppressive therapy, cancer-related chemotherapy or radiation therapy in the past 12 months.

History of hypersensitivity to the investigational products.

Likelihood of requiring treatment during the study period with drugs not permitted by the clinical study protocol.

Clinically relevant cardiovascular (s.p. cardiac infarction, coronary heart disease (CHD), treatmenresistant hypertension, thromboembolic disease, thromboembolic events shortly before admission), hepatic (Child B or C liver disease), endocrine (morbid obesity (BMI > 40)) or systemic (cancer) disease (malignoma).

Epileptiform diseases.

Phenylketonuria.

HIV disease, AIDS.

Informed consent missing.

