The fact that no increase in hemoglobin, hematocrit, reticulocyte or erythrocyte count was found in either study is an especially interesting aspect regarding the treatment of burned patients; besides the well-known fact of decreased EPO efficacy regarding erytropoiesis in inflammation and in trauma situations of the organism, no explanation for this phenomenon has been given so far.

Known complications of EPO treatment are thromboembolic events. A large multi-center trial investigating the safety of EPO administration to poly-traumatized patients demonstrated EPO is safe and beneficial for these patients and that thromboembolic events were reduced to ranges seen in poly-traumatized patients not receiving EPO when combined with an appropriate anti-thrombotic therapy
[38]. As the thromboembolic risk of thermally injured patients is comparable to that of poly-traumatized patients, we conclude that EPO administration in thermally injured patients is safe when combined with an adequate anti-thrombotic prophylaxis as it is done in our trial.

There are two further well-known adverse events related to EPO. The first is the increase in blood pressure in already hypertonic patients
[39] with the consequence that therapy resistant arterial hypertension is an exclusion criterion of the trial. The second is the unclear situation of EPO in patients with malignant tumors. In several trials it was shown that the mortality rate of EPO-treated groups is higher than for untreated controls
[39]. Therefore, a known malignancy is also an exclusion criterion of the trial.

Age, nutritional status, affected total body surface, gender, concomitant illnesses, inhalation injury or other concomitant trauma, as well as wound infections, have a large influence on the patient’s prognosis, survival rate and wound healing. Therefore we considered all of these factors carefully and discussed their relevance for our primary and secondary endpoints. As we are unable to foresee which patient group will profit most, we consider an exclusion of one of this groups as unethical.

Dermal thermal traumas are commonly seen in two age groups of adults. The first group comprises young adults aged between 18 and 28 and the second group comprises elderly persons aged over 65 years. As we are not able to foresee which of these groups would benefit most from pro-regenerative treatment, we decided to include patients aged 18 to 75 in our study
[40].

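### For patients over 40, the exclusion list makes 60% burned area a floor while the population section makes it a ceiling, so read literally only exactly 60% is eligible

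*Protocol article*

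**What the plan says.** Three places in the protocol article bear on burned area and age.

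- **Patient population** admits adults with "scalding injuries between 5% and 60% of total body surface (TBS"), and adds in parentheses that "patients under 40 can have more than a 60% TBS injury". For patients who are not under 40, 60% is therefore the upper limit.
- **Exclusion criteria** contain, run together with the body-weight item, a line on total "burn surface area involved less than 60% in patients older than 40 years of age". As an exclusion, it makes 60% a lower limit for the older group.
- **Exclusion criteria, next line:** "In patients below 40 years of age no limitation of maximum burned body surface and no limitation of ABSI score will be considered".

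Three further statements give context. The exclusion list removes, for the same age group, "Estimated survival shorter than one week (abbreviated burn severity index (ABSI) > 12) in patients older than 40 years of age". The Inclusion criteria give the age range as "Men and women, age ≥ 18 and ≤ 75 years" and contain no burned-area item. The Discussion names people over 65 as one of the two adult age groups in which burns are common, and concludes that "we decided to include patients aged 18 to 75 in our study".

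**The concern.** The two sections set the same threshold for the same patients in opposite directions. A 50-year-old with a 20% burn qualifies under Patient population and is barred by the exclusion list. A 50-year-old with a 70% burn is outside the range in Patient population and is not barred by the burned-area exclusion line.

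Eligibility defines who is randomized and to whom the result applies. The Discussion says that age and affected body surface have a large influence on prognosis, survival and wound healing, and the primary endpoint is a healing time. If centers worked from conflicting text, they could enrol different populations. The planned adjustment for hospital would not settle which population the trial was meant to study.

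**Working it through.** No figure in the plan is computed from the burned-area limits, so the check is one of set logic. Burned area is taken in whole percent, for patients older than 40.

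**Inputs**

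- A = burned area allowed by Patient population for age over 40: 5% to 60%, which is 60 − 5 + 1 = 56 whole-percent values.
- B = burned area removed by the exclusion line for age over 40: below 60%.

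**Step 1. Both sections applied as written.** Eligible = A and not B = {5, …, 60} with {0, …, 59} removed = {60}. One of 56 values remains.

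**Step 2. Exclusion list alone, as written.** Eligible = 60% to 100%, less those removed by the ABSI > 12 line. All patients over 40 with less than 60% burned are again out.

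**Step 3. Inequality reversed (exclude above 60%).** Eligible = {5, …, 60}: all 56 values, in full agreement with Patient population.

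**Step 4. Line read as an inclusion statement in the wrong list (require below 60%).** Eligible = {5, …, 59}: 55 of 56 values. This agrees with Patient population except at exactly 60%.

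**Individual cases for this threshold**

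| Patient | Patient population | Burned-area lines of the exclusion list, as written |
|---|---|---|
| Age 50, 20% burned | eligible | excluded |
| Age 50, 60% burned | eligible | not excluded |
| Age 50, 70% burned | not eligible | not excluded |
| Age 30, 70% burned | eligible | not excluded |
| Age exactly 40, 70% burned | not eligible (not under 40) | neither line applies |

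**Which of the two sections is out of line?** The article's other statements point to a maximum:

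1. Freeing patients below 40 from a maximum makes sense only if older patients have one.
2. The ABSI line removes the most severely injured of the over-40 group. The burned-area line as written removes the less extensively burned of that group.
3. The Discussion explains why ages up to 75 were kept in, and regards excluding patient groups as unethical. The literal line would shut out nearly the whole burned-area range for everyone over 40.

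**Sample size.** The calculation uses only the difference (4 days), the SD (6 days), two-sided alpha 0.05 and power 0.90: n = 2 × (1.960 + 1.282)² × 6² / 4² = 2 × 10.51 × 2.25 = 47.3, rounded up to the stated 48 per group. Burned area does not enter, so no repair of this line changes it.

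**The case against.** The strongest reply is that the line is misplaced, not inverted. The sentence after it is itself an eligibility statement sitting in the exclusion list, and the disputed line reads naturally as its partner: below 60% for those over 40, no maximum for those below 40. The absence of a burned-area item from the Inclusion criteria fits that account. This stands as an explanation, and the article alone cannot decide between the two. It does not rescue the text, because under the heading Exclusion criteria the line still says the opposite of Patient population.

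A second reply is that the intent can be recovered from the article and that sites work from a separate, detailed study protocol, to which the article refers. This also stands, and it limits what can be concluded. Several stronger readings are tempting but unsupported:

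- **That almost nobody over 40 can be or was enrolled.** This describes the literal text, not practice. Nothing shows that the wording reached the sites or that any patient was misclassified.
- **That the trial keeps the most severely burned older patients.** This follows only if the exclusion list is read without Patient population, which bars anyone over 40 above 60%. Even then the ABSI line removes some of them.
- **That such patients are the least likely to give a valid donor-site healing time.** The article gives no rate or source for this.
- **That 35 of the 58 admissible years of age (41 to 75 out of 18 to 75) measures the share affected.** It counts years of age, not patients, and the article gives no age or burn-size distribution.
- **That the 5% minimum is missing.** Patient population states it, and its exception lifts only the upper limit.

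Age exactly 40 is a matter of tidiness and not a second contradiction: Patient population caps such a patient at 60%, and the silence of the exclusion list does not undo that.

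**Conclusion.** The point holds as an error in the text. For patients over 40, the exclusion line contradicts the Patient population section and does not fit the line that follows it. Literally combined, the two sections admit 1 of 56 whole-percent values. With the line reversed they admit 56, and with it read as an inclusion statement 55. The literal result also contradicts the stated decision to include ages 18 to 75.

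The conclusion assumes that the line is an exclusion because it stands under that heading, and that both sections are meant to apply together. The missing line break before it does not affect the inequality. How many patients are affected cannot be stated from the article. Whether the full protocol has the same wording is unknown. A correction is needed because eligibility must be unambiguous, not because harm to the trial has been shown.

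**What to change.** Reconcile Patient population and Exclusion criteria against the approved full protocol, so that the over-40 burned-area limit runs in the same direction in both. There are two ways to do this:

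- reverse the inequality in the exclusion line, so that it expresses the maximum implied by Patient population and by the following line; or
- move the line out of the exclusion list and state it as an inclusion condition. In that case also settle whether exactly 60% qualifies, since the line's wording leaves it out and Patient population takes it in.

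Use one age boundary for the burned-area and ABSI lines and for the exception for younger patients, so that a patient aged exactly 40 is treated the same way throughout. The sponsor should choose the boundary from the full protocol. Changing it in the burned-area line alone would put that line out of step with the ABSI line.

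If the full protocol is already correct, a correction to the article is enough. Only if the same wording reached the sites are a clarifying notice and a check of screening records needed. The cost is a line or two of text, with no extra patients or procedures and no change to the 48 per group.
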